## Abstract

**Background:**

It has been demonstrated that cognitive behavioural therapy (CBT) has a moderate effect on symptom reduction and on general well being of patients suffering from psychosis. However, questions regarding the specific efficacy of CBT, the treatment safety, the cost-effectiveness, and the moderators and mediators of treatment effects are still a major issue. The major objective of this trial is to investigate whether CBT is specifically efficacious in reducing positive symptoms when compared with non-specific supportive therapy (ST) which does not implement CBT-techniques but provides comparable therapeutic attention.

**Methods/Design:**

The POSITIVE study is a multicenter, prospective, single-blind, parallel group, randomised clinical trial, comparing CBT and ST with respect to the efficacy in reducing positive symptoms in psychotic disorders. CBT as well as ST consist of 20 sessions altogether, 165 participants receiving CBT and 165 participants receiving ST. Major methodological aspects of the study are systematic recruitment, explicit inclusion criteria, reliability checks of assessments with control for rater shift, analysis by intention to treat, data management using remote data entry, measures of quality assurance (e.g. on-site monitoring with source data verification, regular query process), advanced statistical analysis, manualized treatment, checks of adherence and competence of therapists.

Research relating the psychotherapy process with outcome, neurobiological research addressing basic questions of delusion formation using fMRI and neuropsychological assessment and treatment research investigating adaptations of CBT for adolescents is combined in this network. Problems of transfer into routine clinical care will be identified and addressed by a project focusing on cost efficiency.

**Discussion:**

This clinical trial is part of efforts to intensify psychotherapy research in the field of psychosis in Germany, to contribute to the international discussion on psychotherapy in psychotic disorders, and to help implement psychotherapy in routine care. Furthermore, the study will allow drawing conclusions about the mediators of treatment effects of CBT of psychotic disorders.

**Trial Registration:**

Current Controlled Trials ISRCTN29242879

## Background

### Positive symptoms and cognitive behavioural therapy

In the last two decades cognitive behavioural therapy (CBT) approaches for patients with schizophrenia have been developed which are specifically designed to reduce severity of positive symptoms. Positive symptoms such as persecutory delusions and hallucinations, which interfere with the patient's ability to maintain social relationships, cause serious distress and life disruption in patients as well as in relatives. They represent hallmark symptoms of psychosis in the schizophrenia spectrum disorders. Even with advances in pharmacological treatments for schizophrenia and other psychotic disorders there is a large subgroup of patients characterised by nonresponse to antipsychotic treatment. Leucht et al. [1] report nonresponse rates between 38% and 76% even when second generation antipsychotic agents are prescribed.

Against this background the investigation of other treatment approaches which may have the potential to reduce positive symptoms has high priority. It has been demonstrated that cognitive behavioural treatment (CBT) has a moderate effect on symptom reduction and on general well being of patients suffering from psychosis. The most recent meta-analyses [2,3] state that the effect size of CBT is .37 for the reduction of positive symptoms. Based on the earlier meta-analysis of Pilling et al. [4] the British National Institute of Clinical Excellence recommended CBT for routine care. In the meantime, also in other countries like Germany [5], CBT is a recommended treatment modality for symptom reduction.

### Open questions

However, many important questions remain unanswered, even if the efficacy of CBT for symptom reduction is increasingly well established.

1. CBT for psychosis has been specifically developed for the reduction of positive symptoms. However, in contrast to more recent meta-analyses the Cochrane meta-analysis of Jones et al. [6] did not find significant reduction of positive symptoms indicating that more large scale clinical trials are needed. Wykes et al. [2] showed a significant heterogeneity in their meta-analysis which might point to unknown moderator effects. In particular the evidence for the specific efficacy of CBT should be improved. When compared to Supportive Treatment, CBT could not as yet demonstrate clear superiority.

2. Patients with psychotic disorders might conceivably experience symptom exacerbation or suicidal crises as a consequence of psychotherapeutic efforts. Negative effects should actively be sought in order to demonstrate safety of the treatment. Therefore, Jones et al. [6] recommended investigating adverse events in CBT trials. However, Tarrier et al. [7] investigated suicidality in CBT-trials and did not find any indication for an increased rate of suicide attempts. More data about treatment safety would be helpful for implementation of CBT, as scepticism among clinicians is widespread.

3. Wykes et al. [2] found that outcome in CBT trials is associated with methodological rigor. Thus, more clinical trials applying rigorous methodology are needed in order to investigate whether treatment effects are stable even in high quality studies.

4. Psychotic disorders, in particular schizophrenia, are causing a considerable economic burden, e.g. in terms of costs of care. As resources for health care a limited, the cost-effectiveness of single health services increasingly gains importance. CBT for psychotic symptoms is currently not available for a majority of patients due to therapeutic scepticism and limited resources. Against this background the question of cost-effectiveness should urgently be addressed.

5. Psychological theories of delusions emphasize either altered attention (selectively attending to evidence in favour of the delusions), or disturbances in making unbiased inferences [8]. There are findings that patients with persecutory delusions preferentially attend threat related stimuli or threat to the subject's self concept [9,10]. Theory-of-mind skills and attributional style together with social perception (i.e. social cue perception and facial affect recognition) are considered as the main sub-processes of social cognition [11]. The evidence in support of these hypotheses is limited and should be increased.

6. The identification of moderators and mediators of treatment effects is a major issue for further development of treatment strategies. However, it has as yet not been studied whether CBT, if successful, alter these biases towards normality [12], and whether the success of CBT critically depends on cognitive and social-cognitive skills. Treatment effects on neurocognitive plasticity have thus far only been described for "cognitive remediation" therapy in one fMRI working memory study with 6 patients. After therapy, a differential activation in the lateral frontal lobe has been demonstrated [13]. Well described cognitive limitations or deficits, e.g. of declarative memory and attention span, arise from enduring (trait) and transient (state) neurobiological alterations in schizophrenia patients, with considerable variation being present between subjects. Such cognitive limitations underlie the development of specific symptoms [e.g. delusions, [14]], are correlated with the degree of insight [15], and are limiting the success of any therapy which, like CBT, is based on verbal learning and requires sufficient attention. Process-outcome research in psychotherapy represents an empirical strategy for determining, which aspects of the therapeutic process are particularly helpful or harmful to patients [16]. This research links the two domains of process and outcome studies. Orlinsky et al. [16] view the therapeutic contract (treatment model, e.g. rational, goal setting, format), the therapeutic operations (therapist interventions), and the therapeutic bond (therapist's and patient's interpersonal behaviour) as the essential factors of the treatment process. These factors were empirically found to be linked with therapy outcome in many psychiatric disorders. However, regarding psychotherapy in psychotic disorders, such findings are still missing up to now. With respect to CBT for positive symptoms in psychotic disorders process-outcome research is not yet a major focus. Studies on this topic focus mainly on effectiveness [e.g. [17-19]].

### Objectives

The major objective of this trial is to investigate whether CBT is specifically efficacious in reducing positive symptoms when compared with non-specific supportive treatment (ST) which does not implement CBT-techniques but provides comparable therapeutic attention.

The trial is accompanied by research addressing (a) process-outcome-relationship dedicated to illuminating the question of the active ingredients in CBT and (b) neurobiological factors of delusion formation using functional magnetic resonance imaging (fMRI) and neuropsychological assessment, as well as (c) treatment research investigating adaptations of CBT in adolescents. Finally (d) problems in relation to disseminating and establishing findings in routine care will be identified and addressed by a project on cost-effectiveness.

## Methods/Design

### General design aspects

This study is a multicenter, prospective, single-blind, parallel group, randomised clinical trial (principal investigator(PI): SK), comparing CBT and ST with respect to the efficacy in reducing positive symptoms in psychotic disorders at nine months after inclusion. The study includes patients with persistent positive symptoms in six study centers applying a systematic recruitment strategy. CBT as well as ST consist of 20 sessions altogether, 165 participants receiving CBT and 165 participants receiving ST (Table 1). The duration of treatment for each study patient will be approximately 36 weeks (i.e., 9 months). The study will be conducted in accordance to GCP and CONSORT. The study has received approval from the local ethics committees and is carried out in accordance with the latest version of the Declaration of Helsinki.

**Table 1 T1:** Study design

Study condition	CBT Cognitive Behavioural Therapy (+ standard care)	ST Supportive Treatment (+ standard care)
Major inclusion criteria	Patients with psychotic disorders, PANSS-Delusion or - Hallucination ≥ 4, symptoms persistent for at least 3 months	

N = 330 (to be included in six study centres)	165	165

Study treatment sessions (treatment duration 9 months)	20	20

Primary Outcome	Positive Symptoms (PANSS) at post treatment assessment (nine months after inclusion)	

post treatment follow-up	24 month	

### Process of recruitment and obtaining written informed consent

The recruitment for this study will address the catchment area of the participating institutions (Departments of Psychiatry and Psychotherapy of the Universities of Bonn (PI: MW), Düsseldorf (PI: WW), Essen (PI: BM and GS), Frankfurt (PI: GW and JH), Köln (PI: AB), and Tübingen (PI: SK) with their associated inpatient and outpatient facilities). It aims at implementing a systematic recruitment plan which will be documented according to CONSORT. For every screened patient the inclusion and exclusion criteria will be recorded. All patients who fulfil the inclusion criteria will be offered to participate in this study. Thus, the resulting sample should represent a geographic cohort.

Under conditions of routine care the patient population addressed by this trial is treated in psychiatric hospitals in case of acute exacerbations, and psychiatric outpatient facilities. In addition, patients are cared for by a considerable number of social psychiatric institutions for supported housing, supported work, and other social psychiatric services.

For the duration of the recruitment phase all inpatients of the participating institutions with psychotic disorders will be screened for their eligibility before discharge from hospital. Information about the study will be provided to the respective patients whenever possible. At the same time a detailed assessment of eligibility will take place. In outpatient departments a complete screening will be conducted for intervals of three months in order to implement comparable strategies for systematic recruitment. In addition, recruitment can also take place in other outpatient services and practices as well as in institutions for supported housing or supported employment. Again, systematic recruitment strategies will be applied.

The registration procedure will be conducted for all patients with a tentative diagnosis of a psychotic disorder (see Figure 1, 2, 3). Patients without "obvious" exclusion criteria (e.g. age, foreign language, living outside of the catchment area, substance dependency as primary problem, mental retardation, ongoing outpatient psychotherapy) will be approached and offered to be informed about the study.

**Figure 1 F1:**
[figure not shown]
**Process of screening**.

**Figure 2 F2:**
[figure not shown]
**Informed consent and baseline examination (T0)**.

**Figure 3 F3:**
[figure not shown]
**Randomization and begin of study therapy**.

In case of refusal, the patient will be asked whether he is willing to give reasons for refusal and to allow for symptom assessment (PANSS) at the time of refusal. For this purpose a separate patient information and consent form will be applied. Only after giving consent for this interview the reasons for refusal from the viewpoint of the patient and the current symptomatic status will be assessed and recorded. If the patient does not give his consent to be interviewed for his reasons of refusal, the staff member who has provided the information about the trial will give his opinion about the major reason.

In a first appointment potentially eligible patients will be informed about the study using the written patient information. In in-patients study information can be provided in the hospital. The written patient information will be handed out when the patient signifies interest in study participation. In each case, obtaining written consent will take place at the beginning of a second appointment prior to inclusion examination. This second appointment has to take place in an out-patient setting in order to ensure the patient's willingness to start outpatient treatment. If patients have by law a care giver responsible to provide support for the patient regarding health related decisions, patients can only be included in the trial if both the patient and the care giver give their informed consent. The care giver will be asked to show the staff member responsible for inclusion his/her certificate of appointment.

For every screened patient a paper based screening and randomisation form will be filled in and faxed to the Coordination Centre of Clinical Trials (CenTrial). The screening and randomisation form will include a list of questions to be answered during the registration procedure. In particular, the inclusion and exclusion criteria will be recorded. Patient screening and randomisation will only be accepted from authorized investigators. At the end of the screening and randomisation form the investigators will document the intended status of the patient in the trial: (1) as patient to be included and randomised, or (2) as patient not to be included but screened (with or without participation in the refusal survey).

### Inclusion Criteria

In order to be included into the study, patients have to meet diagnostic criteria of schizophrenia (DSM-IV 295.1, 295.2, 295.3, 295.6, 295.9), schizophreniform disorder (DSM IV, 295.4), schizoaffective disorder (DSM-IV 295.7), or delusional disorder (DSM IV 297.1), confirmed by a structured clinical interview (SCID-I). Essential for inclusion is moderate or severe symptom intensity, i.e., a score of 4 or more, on the PANSS-items "Delusions" (P1) or "Hallucinations" (P3). Furthermore, the presence of positive symptoms for at least three months with or without compliance regarding antipsychotic medication is necessary. Other inclusion criteria are fluency regarding the German language, age between 18 and 59, a verbal IQ > 80 assessed by a multiple-choice vocabulary test ("Mehrfachwahl Wortschatz Intelligenz-Test", MWT-B, [20]), and willingness to give informed consent. Criteria for exclusion are any kind of organic brain diseases (other than schizophrenia) according to standard patient examination procedures and diagnosis of substance abuse or substance dependence according to DSM-IV/SCID-I as primary clinical problem.

### Randomization

All patients who give consent for participation and who fulfil the inclusion criteria will be randomized. Randomisation will be requested by the staff member responsible for recruitment and clinical interviews from CenTrial.

In return, CenTrial will send an answer form to the study therapist who is not involved in assessing outcome of the study. This form will include a randomisation number. In every centre closed envelopes with printed randomisation numbers on it are available. For every randomisation number the corresponding code for the therapy group of the randomisation list will be found in inside the envelopes. The therapist will open the envelope and will find the treatment condition to be conducted in this patient. The therapist then gives the information about treatment allocation to the patient. Staff responsible for recruitment and symptom ratings is not allowed to receive information about the group allocation.

As part of the efforts of quality assurance the correctness of the randomisation procedure in each patient will be monitored at the regular on-site visits.

The allocation sequence will be generated by the Institute for Medical Biometry (IMB) applying a permuted block design with random blocks stratified by study centre and medication compliance (favourable vs. unfavourable). The blocks should provide comparable numbers of patients in both conditions at any time in the course of the study. The block size will be concealed until the primary endpoint will be analysed. Throughout the study, the randomisation will be conducted by CenTrial in order to keep the data management and the statistician blind against the study condition as long as the data bank is open. The randomisation list remains with CenTrial for the whole duration of the study. Thus, randomisation will be conducted without any influence of the principal investigators, raters or therapists.

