On this background we aim to identify an effect size of more than .35 as significant given an anticipated drop out rate of 20%. An ES of .35 would be obtained if the PANSS Scores (Positive Syndrome) at the post treatment assessment were 12 for CBT and 14.5 for ST with a standard deviation of 7.14. An ES of less than .35 would be of limited clinical relevance.

This results in n = 130 per group for a power of 80% and a two-sided significance level of 5% (sample size calculated by nQuery 4.0, Panel MGT0). The confirmatory statistical analysis will be based on the intention-to-treat principle. Patients with missing PANSS-scores at T9 (post-treatment) will be included with the last observation carried forward (LOCF). In case of missing PANSS-scores at T9 the treatment effect will presumably be underestimated by using LOCF. To compensate for this underestimation the sample size should be adapted for drop out. Thus, we plan to include 330 patients (165 per study condition).

As assumptions about the real effect size cannot be based upon the literature we calculated different scenarios: in case of a lower effect size and/or drop out of more than 20% the statistical power will be reduced. For example, a reduced ES of 0.2 would result in a power of only 36% for the drop out of 20%. An increased drop out of 30%would reduce the power to 74% for the minimum ES of .35. On the other hand, a more favourable ES of 0.45 would increase the power to 85% for the maximum drop-out rate of 20%.

With a sample size of 330 individuals (165 each therapy group), ten assessments per patient, one primary analysis variable (therapy) and one covariable (center), the power should also be sufficient for a Mixed Model [42].

Table 3 gives an overview over the number of patients required in the different stages of the trial and the required effort for treatment and assessment. In order to successfully include 330 patients 6 study centers have been included which were committed to participate actively in this trial.

**Table 3 T3:** number of patients required in the different stages of the trial

	total	per center
required number of eligible patients (with 75% refusal)	1304	217
number of patients to be included (incl. 20% drop out)	330	55
number of patients to be analysed (ITT, LOCF)	330	55
number of patients to be analysed per protocol	260	44
treatment sessions (CBT and ST)	5530	922
number of visits	4620	770

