### Statistical Analysis

The primary endpoint for the biometrical evaluation (responsible statistician: CM) is the PANSS-Positive-Score of the Positive and Negative Syndrome Scale at the time of 9 months after inclusion. It will be analysed after completion of T9-assessments.

The statistical hypothesis for the confirmatory test of the primary endpoint is that the treatment groups are significantly different when analysed using multilevel linear mixed models with treatment and study centres as levels of analysis and adjustment for baseline values. The decision for maintaining or rejecting the null hypothesis will be made applying a two-sided test with α = 0.05. A two-sided test will be chosen as the published results about the comparison of CBT and ST are inconsistent. The observed effects will be described by use of means including the appropriate (one-sided) 95%-confidence intervals.

The confirmatory statistical evaluation of the efficacy of the CBT in this trial will be restricted to the primary endpoint. Only the rejection of the null hypothesis will be interpreted as statistical evidence for the efficacy of CBT. The confirmatory statistical analysis will be based on the intention-to-treat principle (ITT). In addition, a "per protocol" (PP) analysis will be conducted

All secondary endpoints will be compared and statistically assessed for descriptive purposes and not in a confirmatory sense. The aim of the analysis is explorative data analysis, not hypothesis testing or generation of evidence for efficacy. Because of the explorative character of this part of the analysis, no a priori statistical analysis plan exists. If adequate, secondary endpoints will be compared and statistically assessed using covariance techniques with baseline values and centers as covariates. Changes of scores over time will be modeled using linear or non-linear or nonparametric models as adequate. In addition, appropriate statistical methods of explorative data analysis including graphical methods and descriptive statistics will be used. No interim analysis and no subgroup analyses are planned.

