### Medication

Regarding psychopharmacological treatment the study is open and requires no restriction of treatment. The sample size of this trials justifies the expectation of equal distribution of type (classical vs. atypical antipsychotics), dose, rate of non-adherence to medication, prescription of other psychopharmacological treatment (antidepressants, mood stabilizers, benzodiazepines) in both treatment groups.

However, both the medication dose and the medication compliance are potential confounders which have to be controlled for. In particular, it could be the case that medication will not be completely independent from the study condition. As medication has the potential to influence the course of symptoms it is important to observe the medication carefully to allow for detailed analysis of this aspect. Medications and doses will be documented monthly. Side effects will be assessed at baseline as well as at the post-treatment assessment T9.

Medication compliance [43] will be rated monthly along a 7-point scale (with 1 = total rejection of medication, and 7 = active cooperation and full acceptance of medication).

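### Medication compliance, one of the two randomisation stratifiers, is not named in the confirmatory model, which makes the test slightly conservative

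*Protocol article*

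**What the plan says.** - Protocol article, Randomization: the allocation list is generated "applying a permuted block design with random blocks stratified by study centre and medication compliance (favourable vs. unfavourable"), so there are two stratifying factors, centre (six sites) and a binary compliance factor.
- Protocol article, Statistical Analysis: the confirmatory comparison uses "multilevel linear mixed models with treatment and study centres as levels of analysis and adjustment for baseline values", with a "two-sided test with α = 0.05". Compliance is not named.
- Protocol article, Sample size calculation: the remark that power should also suffice for a mixed model counts "one primary analysis variable (therapy) and one covariable (center"). The planned size itself comes from a simple two-group comparison: "This results in n = 130 per group for a power of 80% and a two-sided significance level of 5"%, with assumed PANSS scores that "were 12 for CBT and 14.5 for ST with a standard deviation of 7.14".
- Protocol article, Medication: "both the medication dose and the medication compliance are potential confounders which have to be controlled for". Compliance on study "will be rated monthly along a 7-point scale", and the section says medication may come to depend on the study condition.

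**The concern.** A factor is normally made a stratifier because it is expected to predict outcome. Balancing the arms within its levels takes most of its contribution out of the difference between arms. A model without that factor still counts its contribution as residual noise, so the reported standard error overstates the real sampling variation of the treatment estimate. The test then rejects less often than its nominal level under the null, and some power is given up.

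The sample size section calculates 80% power at an effect size of 0.35 and concedes 74% if drop-out reaches 30%. A small, avoidable loss is therefore worth removing, particularly since the plan carries one stratifier into the model and gives no reason for leaving out the other.

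**Working it through.** **Inputs.** From the protocol article: means 12 and 14.5, SD 7.14, two-sided alpha 0.05, n = 130 per group, 330 patients in total, six centres by two compliance levels. Not in the document: R², the share of residual nine-month variance (after the other model terms) that the compliance stratum explains. I assume 2% to 10%.

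**The plan's own figure.** Effect size = 2.5 / 7.14 = 0.350. The normal approximation, n = 2(1.960 + 0.842)² / 0.350², gives 129 per group. The exact t-test gives 130, with power 80.3%. The stated 130 is reproduced.

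**Formulas.** With balance within strata, the true variance of the treatment estimate is (1 − R²) times the variance reported by the model without the stratum. Write f = √(1 − R²) and δ = 0.35 × √(130/2) = 2.822.

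- Factor by which the model standard error is too large: 1/f
- True alpha, stratum omitted: 2[1 − Φ(1.96/f)]
- Power, stratum omitted: Φ((δ − 1.96)/f)
- Power, stratum included: Φ(δ/f − 1.96)

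Example for R² = 0.10: f = 0.949. True alpha = 2[1 − Φ(2.066)] = 0.0388. Power omitted = Φ(0.862/0.949) = 81.8%. Power included = Φ(2.975 − 1.96) = 84.5%.

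| R² (assumed) | SE too large by | True alpha | Power, omitted | Power, included | Gain (points) |
|---|---|---|---|---|---|
| 0 | 0% | 5.0% | 80.6% | 80.6% | 0 |
| 0.02 | 1.0% | 4.8% | 80.8% | 81.3% | 0.5 |
| 0.05 | 2.6% | 4.4% | 81.2% | 82.5% | 1.3 |
| 0.10 | 5.4% | 3.9% | 81.8% | 84.5% | 2.7 |

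The power column for the omitted stratum also rises with R², because the design has already reduced the true variance. The fair comparison is therefore across each row, not against a fixed 80%. At 165 per group the gain is smaller: 89.1% to 89.5% at R² = 0.02, and 90.1% to 91.8% at R² = 0.10.

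**Simulation.** Set-up: 330 patients, six centres by two strata, random blocks of 4 or 6, linear model with baseline and centre, with and without the stratum. Assumed: 30% in the unfavourable stratum and a baseline correlation of 0.5. There were 4,000 null runs per row, with a Monte Carlo error of about 0.35 points. The implied R² is 1 minus the squared ratio of the mean model standard errors with and without the stratum.

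| Stratum effect | Implied R² | Null rejection, omitted | Null rejection, included |
|---|---|---|---|
| 0.3 SD | 1 − (0.0954/0.0966)² = 0.02 | 4.8% | 5.2% |
| 0.5 SD | 1 − (0.0955/0.0988)² = 0.07 | 3.7% | 4.3% |
| 0.8 SD | 1 − (0.0954/0.1036)² = 0.15 | 3.4% | 5.3% |

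The direction agrees with the formula in every row. At 0.8 SD the model standard error without the stratum was 0.1036, against an actual spread of the estimates of 0.0968. For a true effect of 0.35, the mean estimate without the stratum lay between 0.3445 and 0.3511.

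**The case against.** **The effect is small and errs on the safe side.** This stands. The omission causes no bias and no excess of false positives. Within the assumed R² range the simulated differences are not much larger than the Monte Carlo error, and only the 0.8 SD case, which lies outside that range, shows a clear gap.

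**The baseline term might already cover compliance.** The wording is general and plural, and Table 2 shows that compliance is assessed at T0. Nor does the count of one covariable settle the matter, because that remark leaves out baseline PANSS as well and so is not a full specification. Even so, baseline PANSS is the natural reading, and a confirmatory model should not leave the question open.

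**This is detail for an analysis plan.** Partly fair. The protocol does, however, state the terms of its confirmatory model itself, and names one stratifier without the other.

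**Stronger readings that the document does not support.**

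- A reader might infer that the standard error ignores the stratification altogether. It does not: centre is in the model, and only the binary factor is unnamed.
- A reader might infer that the model contradicts the Medication section, which says compliance must be controlled for. That section deals largely with medication during the trial, to be observed so that it can be analysed in detail. Nothing in the document places these variables in the efficacy model, and stratification already controls in part for compliance at entry.
- A reader might infer that the Medication section prescribes an adjustment for on-study medication, which could bias the effect. No such analysis is specified.

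**Conclusion.** The point holds as a modest inefficiency. Randomisation is stratified by centre and compliance, and the confirmatory model, on its natural reading, carries only centre. If the stratum explains 2% to 10% of the residual nine-month variance, the true alpha is about 4.8% to 3.9%, and 0.5 to 2.7 points of power are given up at effect size 0.35 and 130 per group. If compliance is not prognostic, nothing is lost.

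The size rests on the assumed R², on near-complete balance within strata, and on taking 0.35 as the effect size relative to the residual SD of the model without the stratum. It would be wrong to set the adjusted power against a flat 80%, which would suggest a gain of up to 4.5 points (84.5 − 80). Nor does the omission make a positive result less credible. The planned sample size does not change.

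**What to change.** In the Statistical Analysis section, name the terms of the confirmatory model: treatment, centre, baseline PANSS positive score, and the binary compliance stratum as a fixed effect. Use the stratum value under which each patient was randomised, not one rebuilt later from the monthly ratings.

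The cost is one degree of freedom and no new data, since the stratum had to be known to allocate each patient. According to the time schedule, analysis of the main outcome starts in November 2010, and the Blinding section withholds the group variable until data checks are complete. The term can therefore be fixed before the statistician sees the allocation.

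Optionally, add a sentence to the Medication section: the confirmatory model adjusts only for this baseline stratum, and on-study dose and compliance, which treatment may change, are analysed separately.
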